### 196 Covariates

197 Age of a child

198 Sex assigned at birth

199 Socio-economic status (based on PCA – total household income, highest parental education, and  
200 neighbourhood quality) (See appendix – page 15)

201 Polygenic scores (See appendix – page 15)

202 20 Principal components to account for the possibility of population stratification within the Add  
203 Health European-ancestry subsample in the same model.

204 Maternal factors (Hypertension, diabetes, placental problems, maternal age, infections, C-section,  
205 alcohol consumptions, tobacco usage, and mental health problems).

206 Multiple correspondence analysis (MCA) will be applied and components with over 60% of variance  
207 will be used.

208 Neonatal factors (Dyspnea, convulsion, jaundice, oxygen support, NICU). MCA will be applied.

209 Child factors (puberty).

210 Scanner sites as recommended by ABCD

211

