## Methods

### Participants

The neuroimaging and behavioural data used in this study will be obtained from the ABCD Study (data release 5.0; <https://abcdstudy.org/>; <http://doi.org/10.15154/1523041>), a longitudinal cohort of 11,875 children born between 2005 and 2009. These children were enrolled at ages 9-11 years from 21 research sites across the U.S. between 2016 and 2018, with the intention of following them for a period of at least 10 years. This recruitment cohort closely matches the sociodemographic composition of the US population of 9-11-year-old children. Most of the children were enrolled through local elementary and charter schools at each data-collection site. A smaller portion was recruited through community outreach and word-of-mouth referrals outside of the school setting. Twins were identified and recruited from birth registries.

During each visit, children accompanied by a parent/guardian, completed a series of measures. These included neurocognitive tests, mental and physical health questionnaires, environmental exposure data collection, providing biological specimens, and participating in brain imaging. All were asked for an in-person assessment session for self- or parent-report of mentioned behavioural measures and for biological specimen collections once a year, with brain imaging conducted biannually. For this study, we will use data collected between 2016 and 2018.

Children were excluded if they were born extremely preterm (< 28 weeks of gestation) or had birth weight (< 1200 g), were not proficient in English, had any neurological problems, had a history of seizures, or had a contraindication to undergo brain MRI scans. All children and their parents/guardians provided informed written consent/assent for participation, and the central Institutional Review Board at the University of California, San Diego approved the study protocols. All the research methods were performed in accordance with the relevant guidelines and regulations.

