## Statistics

Maternal and child characteristics will be summarized using means and standard deviations for continuous variables and frequencies with counts for categorical distributions. To compare the demographic and clinical characteristics between children born preterm, early-term and born at full-term, independent samples t-test and  $\chi^2$ /Fisher exact tests will be employed. Missing covariates will be imputed through multiple imputations by chained equations with the predictive mean matching method using the MICE package in R.

Hierarchical logistic/linear regression model will be used to investigate the relationships between preterm birth and behavioural/brain outcomes. Model 1: Adjusted for age of child, sex, SES, Polygenic scores, 20 PCs, and scanner sites; Model 2: Model 1 + Maternal factors; and Model 3: Model 2 + Neonatal factors; Model4: Model 3 + child factors

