## Appendix

### Socioeconomic status

SES was defined as the first principal component from a probabilistic principal component analysis (PCA), capturing 65% of the variance in total household income, highest parental education, and neighbourhood quality. Children missing more than one of these SES measures were excluded. Household income was determined by the combined annual income of all family members over the past 12 months, categorized as less than \$49,999 (1), \$50,000–74,999 (2), \$75,000–99,999 (3); \$100,000–199,999 (4); and greater than \$200,000 (5). Parental education was categorized into middle school or less (1), some high school (2), high school graduate (3), some college/associate degree (4), bachelor's degree (5), master's degree (6), or professional degree (7). The neighbourhood quality was determined using the area deprivation index, calculated from the American Community Survey using the address of the primary residency. The SES composite and each subcomponent were normalized (mean=0, SD=1).

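### The 60% rule for reducing nine maternal factors by multiple correspondence analysis keeps no, one or about four to six components depending on the reading, and no reading gives full maternal adjustment

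*SAP*

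**What the plan says.** The Covariates section of the SAP lists nine maternal factors: "Maternal factors (Hypertension, diabetes, placental problems, maternal age, infections, C-section", then "alcohol consumptions, tobacco usage, and mental health problems". For this block it states that "Multiple correspondence analysis (MCA) will be applied and components with over 60% of variance" will be used.

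The neonatal line that follows names five factors and the same technique, but no criterion for keeping components: "Neonatal factors (Dyspnea, convulsion, jaundice, oxygen support, NICU). MCA will be applied".

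The Statistics section carries both blocks through the adjusted models: "Model 2: Model 1 + Maternal factors; and Model 3: Model 2 + Neonatal factors; Model4: Model 3 + child factors".

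The SAP does not say whether 60% is a per-component or a cumulative limit, whether inertia is raw or adjusted, how maternal age is cut into categories, or what happens if no component qualifies. Its nearest parallel is the socioeconomic score in the Appendix, a single first component described as "capturing 65% of the variance in total household income, highest parental education, and neighbourhood quality".

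**The concern.** The Hypothesis section claims an independent association between preterm birth and cognition. Model 2 is where the maternal conditions behind preterm birth, such as hypertension and placental problems, are meant to be controlled. Components are instead chosen by how much variance they explain among the covariates themselves. Whatever falls on a discarded axis goes unadjusted, however strongly it is tied to preterm birth or to cognition.

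The rule can also be read in ways that give very different models, and the choice could be made after the results are seen. Finally, MCA works on categories, so maternal age must be cut. No cut-points are given, and age differences within a category would stay unadjusted.

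**Working it through.** **Inputs.** From the SAP: nine maternal and five neonatal factors, the 60% figure (both Covariates), and "a longitudinal cohort of 11,875 children born between 2005 and 2009" (Participants). The SAP gives no prevalences, no correlations and no expected number of components, so there is no stated figure to reproduce. Coding each factor as yes/no is an assumption, relaxed below for maternal age.

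**1. Per component, raw inertia.** Shares sum to 100%, so at most one axis can exceed 60%. For Q binary factors with equal pairwise correlation r, the first share is (1 + (Q − 1)r)/Q. Setting this to 0.60 gives r = (0.6Q − 1)/(Q − 1):

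- Q = 9: (5.4 − 1)/8 = 0.55
- Q = 5: (3.0 − 1)/4 = 0.50

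For nine factors, r = 0.1, 0.2 and 0.3 give first shares of 20%, 29% and 38%.

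The socioeconomic score offers a comparison. Under the same formula, 65% from three variables corresponds to r = (0.65 × 3 − 1)/2 = 0.475. Nine factors at that correlation would give (1 + 8 × 0.475)/9 = 53%, still short of 60%.

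**2. Per component, adjusted inertia.** Benzécri's adjustment keeps axes with eigenvalue λ > 1/Q and rescales each to [Q/(Q − 1) × (λ − 1/Q)]². With equal r > 0, the first axis becomes r² and all others, at (1 − r)/Q, fall away. The first axis then shows 100% whatever r is. At r = 0.1 it passes with a raw share of only 20%.

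**3. Simulation.** MCA was run on n = 11,875 with assumed maternal prevalences of 5 to 50% and one common latent factor. Maternal age had three categories or two.

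| Latent correlation | Maternal age | First raw share | Axes above 60%, raw | First adjusted share (Benzécri / Greenacre) | Axes for cumulative 60% |
|---|---|---|---|---|---|
| 0.1 | 3 categories | 13.7% | 0 | 99.8% / 93.3% | 6 of 10 (63%) |
| 0.3 | 3 categories | 21.9% | 0 | 100% / 98.9% | 6 of 10 (67%) |
| 0.5 | 3 categories | 30.5% | 0 | 100% / 99.1% | 5 of 10 (65%) |
| 0.1 | binary | 15.0% | 0 | 100% / 96.1% | 6 of 9 (69%) |
| 0.3 | binary | 23.2% | 0 | 100% / 99.0% | 5 of 9 (63%) |
| 0.5 | binary | 33.6% | 0 | 100% / 99.0% | 4 of 9 (61%) |

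Even at a latent correlation of 0.9 the first raw share was 55.4% (three categories) or 58.0% (binary).

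**4. Cumulative reading.** Four to six axes stay, holding 61 to 69% of raw inertia, so 31 to 39% is dropped. By construction the rule can drop up to 40%. With binary factors the nine axes together span the same space as the nine factors, so direct entry loses nothing, while keeping four to six axes leaves three to five dimensions out.

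**5. Neonatal block.** No rule is stated. If the maternal rule were borrowed, the first raw share would be 22 to 37% at latent correlations of 0.1 to 0.5 (assumed prevalences 1 to 15%), so none would pass per component. Cumulatively, three of five axes would stay (62 to 71%).

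**The case against.** The strongest reply is that the sentence speaks of components in the plural. Since no more than one can exceed 60% of raw inertia alone, a cumulative rule is the more natural meaning and a common one. This stands. A reader might infer that maternal and neonatal confounders are largely left uncontrolled in Models 2 to 4; the SAP does not support that. On the cumulative reading the maternal block is substantially adjusted for, and the loss is partial.

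Four further objections also stand:

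- **The 60% rule is written for the maternal block only.** The neonatal defect is a missing rule. Those five factors arise after birth and may be consequences of preterm birth, so weaker adjustment for them cannot be assumed to leave confounding.
- **The 0.55 and 0.50 limits are exact only for equal correlations.** Seven of nine factors at 0.8, the rest uncorrelated, give (1 + 6 × 0.8)/9 = 64% with a mean correlation of (21 × 0.8)/36 = 0.47. That pattern is implausible for this list, but an average of 0.55 is not strictly necessary.
- **The bias cannot be put in numbers from the SAP.** Any percentage of confounding left over would follow from effects and correlations chosen by whoever simulates it. The Primary analyses section also does not say which of Models 1 to 4 is primary, so the effect on the primary result is not shown.
- **Estimating individual risk factors is motivation in the Introduction, not one of the two objectives.** It carries no weight here.

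It can also be said that reducing correlated or rare binary factors is a legitimate choice, and that clearer wording would be enough. Clearer wording would make the models reproducible. It would not recover the discarded covariate information, and with this sample size nothing is gained in exchange.

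**Conclusion.** The point holds as a fault in the method as well as in the wording. Depending on the reading, Model 2 gains no maternal term (raw inertia, per component), one axis with about 14 to 34% of raw inertia (adjusted, per component), or about four to six axes with up to 40% of the maternal variance dropped (cumulative). None of these is full adjustment for the nine measured factors, and the SAP does not fix which applies.

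The limit of one axis per component and the 40% ceiling follow from arithmetic alone. The 0.55 threshold assumes equal correlations. The counts of four to six and the 14 to 34% rest on assumed prevalences, a single latent factor and latent correlations of 0.1 to 0.5. The consequence is partial and avoidable residual confounding by maternal factors, of unknown size.

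**What to change.** Delete the MCA step for the maternal block. State that Model 2 adds the nine maternal factors directly, with maternal age continuous or as a spline and the coding of the other eight given.

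If the neonatal block is kept in Model 3, enter its five factors directly too. Describe that model as additionally adjusted for neonatal conditions that may follow from preterm birth, not as controlling for confounders.

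The cost is a change of wording and a few degrees of freedom. For the maternal block it is nine terms against four to six axes, so three to five more, plus any spline terms and any extra levels of a factor. The neonatal block adds five terms. This is negligible with 11,875 children in the cohort and 10,069 after genotyping quality control (Appendix), although the SAP does not state the final analysed number.

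If the sponsor prefers to keep MCA, the second-best course is to state whether 60% is per component or cumulative, the inertia scale, the same rule for both blocks, the cut-points for maternal age, and a fallback if no component qualifies. That fixes the models in advance but still discards covariate information.

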## Statistics

Maternal and child characteristics will be summarized using means and standard deviations for continuous variables and frequencies with counts for categorical distributions. To compare the demographic and clinical characteristics between children born preterm, early-term and born at full-term, independent samples t-test and  $\chi^2$ /Fisher exact tests will be employed. Missing covariates will be imputed through multiple imputations by chained equations with the predictive mean matching method using the MICE package in R.

Hierarchical logistic/linear regression model will be used to investigate the relationships between preterm birth and behavioural/brain outcomes. Model 1: Adjusted for age of child, sex, SES, Polygenic scores, 20 PCs, and scanner sites; Model 2: Model 1 + Maternal factors; and Model 3: Model 2 + Neonatal factors; Model4: Model 3 + child factors

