### Polygenic Score Derivation and Analyses

#### Genotyping, quality control, and imputation

Saliva samples were collected from all the children during the T0 visit and genotyped using Rutgers University Cell and DNA repository using the Smokescreen array consisting of 646,247 genetic variants.

Quality control, imputation, and genetic PCA were performed by the National Bioinformatics Infrastructure Sweden (NBIS). The following pre-processing steps were conducted. Briefly, single nucleotide polymorphisms (SNPs) with call rates < 98% or minor allele frequencies (MAFs) < 1% were excluded before imputation. Individuals with high rates of missingness (> 2%) and absolute autosomal heterozygosity > 0.2 were excluded, resulting in 10,069 children and 430,622 genetic variants. Haplotypes were prephased using SHAPEIT2, and genetic markers were imputed using IMPUTE4 software.

We utilized the 1000 Genomes haplotypes—Phase 3 integrated variant set release in NCBI build 37 (hg19) coordinates as reference populations. This dataset consists of 2504 samples and 5008 haplotypes from Europeans, Africans, East Asians, Southern Asians, and Americans ([https://mathgen.stats.ox.ac.uk/impute/1000GP\\_Phase3.html](https://mathgen.stats.ox.ac.uk/impute/1000GP_Phase3.html)). We used this imputation since it

provides better concordance in diverse human populations. After that, genotypes with an INFO score < 0.3 or MAF < 0.001% were excluded, which yielded 40,637,119 SNPs in a total of 10,069 children.

The PCA module, as implemented in RICOPILI, was used to check for outliers and control population structure. SNPs were pruned so that there was little linkage disequilibrium (LD) between SNPs ( $R^2 < 0.2$ , 200 SNP window: Plink–indep-pairwise 200 100 0.2). LD pruning was repeated until 100 K SNPs were reached. The resulting SNPs were then projected into the PCA. We utilized the first 20 principal components (20PCs) from the genetic PCA.

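### The SAP does not say whether children without quality-controlled genetic data are imputed or dropped (0 to 1,806 children), and no planned model omits the genetic covariates

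*SAP*

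**What the plan says.** - **Source population.** SAP, Participants, describes the data source as "a longitudinal cohort of 11,875 children born between 2005 and 2009". The exclusions listed there do not include a lack of genetic data.
- **Genetic data.** SAP, Appendix, Genotyping, quality control, and imputation, says saliva was taken from all children and genotyped. It then says: "Individuals with high rates of missingness (> 2%) and absolute autosomal heterozygosity > 0.2 were excluded". After genotype imputation the count is unchanged: "which yielded 40,637,119 SNPs in a total of 10,069 children".
- **Use of the genetic data.** SAP, Covariates, lists the polygenic score and the 20 PCs. SAP, Statistics, places both in the first model: "Model 1: Adjusted for age of child, sex, SES, Polygenic scores, 20 PCs, and scanner sites". Models 2 to 4 each build on the one before, so both are in all four.
- **Missing data.** SAP, Statistics: "Missing covariates will be imputed through multiple imputations by chained equations with the predictive mean matching method". No covariate is exempted, and the predictors for the imputation are not listed.
- **Aims.** SAP, Study objectives, asks in both aims how far genetic and environmental factors explain the association between gestational age and cognition.

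**The concern.** Three parts of the SAP bear on a child whose genotype failed quality control, and they do not fit together. Under Participants the child is eligible. Under the appendix the child is excluded, but the text does not say whether from the genetic file or from the regressions. Under Statistics the child has missing covariates, and missing covariates are imputed. Two analysts could follow this SAP faithfully and run the same primary test at 0.05 on samples that differ by up to 1,806 children.

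Each reading has a cost. Under imputation, adjustment for ancestry and genetic predisposition in the affected children rests on non-genetic variables. Under exclusion, usable genotype data become a condition of entry to every result, including the basic gestational-age association, which needs no genotype. The loss by gestational-age band is not given, so a reader cannot see whether the smaller preterm groups are affected more.

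A second gap follows from the model sequence. It starts with the genetic covariates already in Model 1 and then adds maternal, neonatal and child factors. The change from model to model can speak to those later blocks. It cannot speak to the genetic block, because there is no model to compare Model 1 with.

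**Working it through.** The SAP states no analysis sample size and no number of children to be imputed, so there is no stated figure to reproduce. The 10,069 cannot be rebuilt either, because the number removed at each quality-control step is not given. What can be checked is the gap between the two counts.

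Inputs:
- N = 11,875, source cohort (SAP, Participants).
- G = 10,069, children after genetic quality control (SAP, Appendix, Genotyping section).
- k = 1 + 20 = 21 genetic covariates: cogPGS and 20 PCs (SAP, Covariates and Statistics).

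Step 1, children without usable genetic data: N − G = 11,875 − 10,069 = 1,806. As a share of the cohort, 1,806 / 11,875 = 15.2%. This is an upper bound for the analysis, because exclusions for SES, outcome or ancestry would lower it by amounts that the SAP does not give.

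Step 2, the two readings:

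| Reading | Largest possible N | Children with imputed genetic covariates |
|---|---|---|
| The imputation rule covers the genetic covariates | 11,875 | up to 1,806 |
| The appendix exclusion applies to the regressions | 10,069 (84.8%) | 0 |

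The number imputed therefore lies between 0 and 1,806. At the upper end, 1,806 × 21 = 37,926 values are filled in per imputed data set. That is a measure of volume, not of bias.

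Step 3, precision cost of restriction. Assume that the loss is the same in every gestational-age band and that residual variance is unchanged. Interval width then scales with 1/√n, and √(11,875 / 10,069) = 1.086, or about 9% wider.

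Step 4, information available for imputing the genetic covariates. The listed covariates are age, sex, SES, maternal factors, neonatal factors, puberty and site, besides the genetic variables themselves. None is a measure of race, ethnicity or ancestry. Site and SES, which includes an area deprivation index, may carry some ancestry information. Weak predictors is therefore the supportable description.

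Step 5, models with and without genetics. Models 1, 2, 3 and 4 all contain cogPGS and the PCs, so the number of planned models without them is zero.

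**The case against.** The strongest reply is that the appendix already settles the matter. It says that children failing quality control were excluded, and the same verb is used in the Socioeconomic status section for children missing more than one SES measure, where removal from the study is the natural sense. On that reading nothing genetic is imputed. This is a fair reading and it is why the range starts at 0. It does not close the gap: the sentence stands in a description of genotype processing, the SAP nowhere ties it to the regressions, and the imputation rule makes no exception.

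A second reply is that multiple imputation does not need each filled-in value to be close to the truth. With a suitable imputation model and data missing at random, weak predictors mainly increase between-imputation variance and need not bias the gestational-age coefficient. The outcome and auxiliary variables may also be used. This stands. A reader might infer that the imputed PCs would be little better than random draws, leaving no control for stratification, or that the primary estimate would be biased. The SAP does not support either: it does not specify the imputation model, and nothing in it shows that quality-control failure is related to the outcome.

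A reader might also infer that the 1,806 children were never genotyped. The appendix says otherwise: samples from all children were collected and genotyped, and the only removal of children it describes is for quality control.

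A third reply is that a model without genetics is a new analysis, since the genetic covariates are in Model 1 by design. That is so, but the aims ask about genetic explanation, and the planned sequence cannot provide the comparison.

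**Conclusion.** The point holds as an ambiguity with a measurable size, plus a missing comparison. The SAP leaves open whether up to 1,806 children (15.2% of the cohort) have 21 genetic covariates imputed or are left out. It does not follow that the SAP certainly imputes them; the documents support 0 as well as 1,806. If they are imputed, ancestry control in these children rests on weak predictors. If they are dropped, an entry criterion that is not written down applies to every result.

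Separately, and under either reading, the planned models cannot show how much of the gestational-age association the genetic covariates explain.

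The counts rest on two assumptions: that 11,875 is the starting point, and that no ancestry restriction applies. The Covariates and cogPGS calculation sections refer to a European-ancestry subsample of a differently named cohort. If a restriction of that kind is intended, neither 11,875 nor 10,069 is the relevant number, and the 15.2% would need to be recalculated. This should be corrected before analysis. It does not in itself invalidate the primary comparison.

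**What to change.** 1. State that every model containing cogPGS and the 20 PCs is fitted only in children with quality-controlled genetic data, and exempt these 21 variables from the variables that MICE imputes. Other missing covariates can still be imputed as planned.
2. Add a base model without cogPGS and PCs, fitted in all eligible children. Refit the same base model in the genetic subset. The change from the refitted base model to Model 1 then reflects the genetic covariates alone and is not mixed with a change of sample.
3. Report gestational-age band and SES for children in the genetic subset against those left out.

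The cost is a few sentences in the SAP, two extra fits of one model and one descriptive table, all on data already held. The downside is that the genetic models are reported on at most 10,069 children, with the loss of precision shown above.

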In general, cognitive abilities is largely heritable, with heritability estimates reaching upto 70%. Interestingly, the heritability of general cognitive abilities increase significantly from childhood to early adulthood. Prior studies focusing on contribution of the heritability and biological risk factors, such as preterm birth, have mostly adopted familial designs. Previous studies using sibling analysis have investigated the association between gestational age and intelligence quotient (IQ), finding that these associations are independent of shared familial confounders and statistical covariates. While these studies provide initial insight into the effect of biological risk factors, such as preterm birth, accounting for genetic mechanisms underlying with IQ, they have several limitations. First, these designs require assumptions that can sometimes be violated, for example, siblings do not necessarily share 50% of their genes, nor do they necessarily inherit same risk alleles. Second, this approach cannot account for specific environmental effects, such as maternal factors. Therefore, distinguishing environmental factors and conducting separate genotyping would identify specific environmental contributions, which could be targets for improving cognitive outcomes.

81 Previous familial design studies focusing on association between gestational age and IQ, have  
82 primarily focused on general cognition and have not explored individual domains. It is known that  
83 children born preterm show delay in cognitive abilities, but majority of these children perform within  
84 normal range for general cognitive functioning as a group (i.e., they perform 0.5 - 1.0 SD below that  
85 of term-born peers). But, specific functions such as attention, working memory, and processing  
86 speed are often delayed in this cohort, have not been explored.

87  
88 In addition, preterm birth is a syndrome where various causes might act synergistically to its  
89 manifestation. Previous systematic and meta-analyses have assessed numerous non-genetic risk  
90 factors for preterm birth, such as obstetric and medical history, environmental exposures, and  
91 postnatal factors. Exploring the independent contribution of these risk factors on cognitive abilities  
92 could pave the way for risk-specific interventions and enhance our understanding of the mechanisms  
93 related to these outcomes.

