## Study objectives

The aims of this study are two-fold:

- Investigate the association between preterm and early-term births on cognitive outcomes during mid-childhood; and assess the extent to which these associations can be explained by unmeasured genetic and environmental factors.
- Investigate the association between weeks of gestation and cognitive outcomes during mid-childhood; and assess the extent to which these associations can be explained by unmeasured genetic and environmental factors.

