### **Primary analyses:**

- Linear regression model will be used to investigate whether the one-factor (intelligence) differ between preterm birth, early-term birth and full-term birth (presented as standardized beta and 95% CI)

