### **Exploratory analyses:**

Sex and birthweight

Primary analysis will be uncorrected with statistical significance at 0.05. Secondary analysis will be adjusted for multiple comparison corrections.

All analysis will be carried out using R studio.

242 **Planned Figures and Tables**

243 Table 1 Demographics of maternal and child characteristics

244 Table 2 Results from the primary analysis

245 Table 3 Results from the weeks of gestation

246

247 Figure 1 Results of PCs.

248 Figure 2 Outcomes

249

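### The objectives ask what unmeasured genetic and environmental factors explain, but every model adjusts only for measured covariates, and SES and the polygenic score enter at the first step

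*SAP*

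**What the plan says.** Study objectives (SAP) lists two aims, one for the birth groups and one for weeks of gestation. After naming the association, each adds the same task: "assess the extent to which these associations can be explained by unmeasured genetic and environmental factors".

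Statistics (SAP) sets out the model sequence. It opens with "Model 1: Adjusted for age of child, sex, SES, Polygenic scores, 20 PCs, and scanner sites" and continues with "Model 2: Model 1 + Maternal factors; and Model 3: Model 2 + Neonatal factors; Model4: Model 3 + child factors". No crude or age-and-sex model comes before Model 1.

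The primary analysis is a group comparison: "Linear regression model will be used to investigate whether the one-factor (intelligence) differ between preterm birth, early-term birth and full-term birth". The secondary analyses have the same form for other cognitive measures. The exploratory analyses are given in full as "Sex and birthweight". The planned tables cover demographics, the primary results and the weeks-of-gestation results. None is described as showing a change between models.

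**The concern.** To say how much of an association a factor explains, one needs the coefficient with and without that factor. For SES and for the polygenic score, the plan provides only the coefficient with both already in. The score's own coefficient in Model 1 does not fill the gap. It relates the score to cognition and does not show how much of the link between gestational age and cognition the score accounts for.

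The word *unmeasured* raises a second problem. Every term in Models 1 to 4 is a recorded variable or a component built from recorded variables. A regression on these leaves unmeasured factors where they were, in the residual.

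What is at stake is the second clause of each objective. The Introduction motivates the study by the wish to separate genetic from environmental contributions, and the Appendix derives cogPGS in detail. The score then enters where its effect on the gestational-age coefficient cannot be seen. If the analysis starts without a stated base model, someone will have to choose one after seeing results.

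**Working it through.** The SAP gives no figure for attenuation, so there is nothing to reproduce. The check sets the objectives against the models and then illustrates why the planned output cannot settle the question.

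**1. What each step can show** (SAP, Statistics and Covariates)

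| Step | What enters | Change in coefficient available? |
|---|---|---|
| before Model 1 | SES, polygenic score, 20 PCs (with age, sex, site) | No, there is no earlier model |
| Model 1 to 2 | maternal factors | Yes |
| Model 2 to 3 | neonatal factors | Yes |
| Model 3 to 4 | puberty | Yes |

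There are three readable steps, and none is for SES or genetics. SES and the score also enter together, so even a crude model placed before Model 1 would not separate them.

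**2. Whether any analysis addresses unmeasured factors.** The primary, secondary and exploratory analyses contain no family comparison, variance decomposition or bias analysis. The cohort includes twins ("Twins were identified and recruited from birth registries"), but no analysis uses them.

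**3. Illustration.** Let Y = b·E + √h²·G + e, with Y, E and G of unit variance, E coded so that higher means more preterm, and r the correlation of E with genetic predisposition G. The score has squared correlation a² = q/h² with G, where q is the outcome variance that the score explains. Other covariates are ignored. Then:

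- coefficient without the score: c = b + √h²·r
- coefficient with the score: m = b + √h²·r·(1 − a²)/(1 − a²r²)

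From the SAP: h² = 0.70, the upper figure in the Introduction. Assumed, and not in the SAP: q from 0.05 to 0.15, r from 0 to −0.10, and an observed m of −0.10 SD.

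Worked case, q = 0.10 and r = −0.10:

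- a² = 0.10/0.70 = 0.143
- m − b = 0.837 × (−0.10) × 0.857/(1 − 0.00143) = −0.072, so b = −0.028
- c = −0.028 − 0.084 = −0.112
- the score removes 1 − 0.100/0.112 = 11% of c, while the genetic share of c is 0.084/0.112 = 75%

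True effect b behind the same m = −0.10:

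| q | r = 0 | r = −0.05 | r = −0.10 |
|---|---|---|---|
| 0.05 | −0.100 | −0.061 | −0.022 |
| 0.10 | −0.100 | −0.064 | −0.028 |
| 0.15 | −0.100 | −0.067 | −0.034 |

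The genetic share of c is 0% at r = 0, 38 to 41% at r = −0.05 and 71 to 79% at r = −0.10. The part removed by the score is 0%, 3 to 8% and 6 to 15%. With an assumed childhood heritability of 0.40, q = 0.10 and r = −0.10, a² = 0.25, m − b = 0.632 × (−0.10) × 0.75/0.9975 = −0.048 and b = −0.052.

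One Model 1 coefficient is therefore compatible with very different genetic shares, including none. A model without the score would reveal the part the score removes, and nothing beyond that.

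**4. Sample.** The cohort has 11,875 children (Participants) and 10,069 remain after genotype quality control (Appendix). The difference is 1,806, or 1,806/11,875 = 15.2%. A base model fitted to everyone would mix attenuation with a change of sample.

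**The case against.** The strongest reply is that *unmeasured* is a slip. The Introduction criticises family designs and argues for measured factors: "Therefore, distinguishing environmental factors and conducting separate genotyping would identify specific environmental contributions". The hypothesis asks only whether preterm birth is independently associated with cognition, and treating SES and cogPGS as confounders from the start is a coherent way to test that. On this reading the steps from Model 1 to Model 4 answer part of the environmental question, since the maternal factors include alcohol, tobacco, infections and mental health. All of this stands. It does not rescue the SES and genetic parts, because their contribution stays hidden in Model 1 even if the word is corrected.

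Three stronger readings are tempting, and the SAP does not support them.

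- *Neither objective can be answered.* The first clause of each, the association itself, is unaffected by this point, and attenuation by maternal, neonatal and puberty factors is available.
- *The fault is the missing within-family analysis.* The SAP gives reasons for not using a family design. Such an analysis would be one way to keep the word *unmeasured*, but it is not the only repair.
- *Most genetic confounding stays unmeasured because the score captures only 7 to 14% of genetic variance.* That figure is 0.05/0.70 to 0.10/0.70, and the numerator is not in the SAP. The denominator is an upper value ("with heritability estimates reaching upto 70" percent), and the SAP adds that heritability rises with age; at an assumed 40% the same range becomes 12.5 to 25%. More basically, a share of outcome variance is not a share of confounding. With r = 0 there is no genetic confounding at all.

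**Conclusion.** The mismatch is real and can be read directly from the text. Followed exactly, the plan cannot quantify what unmeasured factors explain, and it gives no estimate of attenuation by SES or by measured genetics. This rests only on the wording of the objectives and the content of Models 1 to 4. It does not depend on the illustration, whose score R-squared, exposure-gene correlation and coefficient are all assumed.

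The planned group estimates do not change. A reader might take a coefficient that is stable across Models 1 to 4 as evidence against genetic confounding. The SAP states no such inference, and the models would not support it. The point should be settled before the analysis, because the base model ought to be fixed in advance.

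**What to change.** - In both objectives, replace *unmeasured* with *measured*.
- Before the current Model 1, add a base model with age, sex, site and the 20 PCs. Keeping the PCs in the base treats them as control for population structure and stops them being counted as genetic predisposition.
- Then fit base + SES and base + cogPGS separately, and then both together, which is the current Model 1. Fitting them separately matters because cogPGS draws on an educational-attainment GWAS and SES includes parental education, so a single order of entry would decide how their shared part is credited.
- Fit all models to the same genotyped children.
- Report the change in each gestational-age coefficient (birth groups and weeks) at each step with a confidence interval, computed so that it is compatible with the planned multiple imputation.
- State that residual genetic and environmental confounding is not identified. An E-value or similar bound may be added.

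The cost is three extra models shown as a few table rows, an interval for each change, and a narrower claim. No new data are needed. If the sponsor prefers to keep *unmeasured*, the SAP has to name a method for it, such as a sibling or twin comparison or a quantitative bias analysis.
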